### Dissemination

2.11

The results of this study will be registered on clinicaltrials.gov, and will be published in an academic paper.

## Discussion

3

Our study aimed to establish a prospective registry of 1000 patients to overcome the limitations of Korean integrative medicine or CAM-related research, which involved a small number of patients or a large number of retrospective patients, and to confirm the safety and efficacy of Korean medicine treatment for lumbar disc herniation. Additionally, the effect of the treatment was not only observed immediately after the treatment, but also 6 months after, to analyze the long-term treatment effect of Korean medicine treatment for LDH, which is common in recurrence of chronic pain. Also, as a large number of patients were recruited, we can analyze whether the treatment effect differed among CAM inpatient and whether individual characteristics such as age, sex, and presence of stenosis and accompanying diseases influenced the time of improvement. This study was designed as the first project of the Joint and Spine Pain Integrative Evaluation registry (J-SPINE) project, and in the future, we plan to build a registry for other spinal and joint diseases.

However, the limitation of this study is that it will be conducted without a control group. Although the data on safety can be collected in large numbers, those on effectiveness may be limited due to the absence of the comparison group. However, we plan on recruiting outpatient patients or patients receiving nonintegrated Korean medicine treatment through other registry studies. Through this, it will be possible to check whether inpatient Korean medicine treatment is more effective than the outpatient treatment and on which patients it would be more effective towards. Moreover, if the analysis is carried out according to whether there is a difference in the effects depending on the presence of stenosis and whether the treatment was accompanied with Western medical conservative treatment (eg, analgesic drug treatment, electrophysical treatment, and so on), it is possible to analyze the advantages of combination treatment even without the control group. Additionally, we can analyze whether there is a difference in treatment effects according to age or sex.

Another limitation is that 1000 patients may be large in recruitment but lack safety aspects; during hospitalization, systematic investigation will be conducted with Korean medical doctors investigating and recording the side effects on a daily basis, but in terms of safety, it can be a small number to collect rare events. However, if the system is established and the registry research is expanded through this study, it can serve as a foundation to accumulate safety data in the future.

Additionally, it is expected that there will be many dropouts, as the protocol is configured so that many people with <7 days of inpatient treatment will be withdrawn or drop out. In reality, some patients are admitted for examination and treatment just for insurance benefits if private insurance only supports those with hospitalization, and those with severe initial pain and movement restrictions may improve quickly and will be hospitalized and discharged in a short time. In these cases, hospital stays tend to be shorter. Although we tried to establish a registry to properly validate the efficacy of Korean medicine treatment and exclude inpatients from the test, there may be possibilities where the rate of dropouts is high or the information about the late adverse events in dropout patients is missing. We plan on thoroughly reviewing the reasons for dropouts and revisit those patients with adverse effects during hospitalization.

The strength of this study is that it seeks to recruit many patients, as many as 1000. It is also the first study to prospectively recruit those going through CAM inpatient treatment to examine its efficacy and safety in many people. We will not only confirm the safety and efficacy of integrative Korean medicine treatment in 1000 LDH patients but also analyze whether the individual characteristics such as presence of stenosis, sex, age, and type of disc hernia can affect the treatment. This study is expected to not only provide the basis for validating CAM treatment but to also establish the basis for safety, which has been lacking in the past.

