## Abstract

We developed a protocol for a prospective registry to prove the effectiveness and safety of integrative Korean medicine treatment for inpatients with sciatica due to lumbar intervertebral disc herniation. We plan on recruiting 1000 inpatients receiving integrative Korean medicine treatment for lumbar intervertebral disc herniation at four spine specialized Korean medical hospitals. Patients enrolled in the registry will be evaluated at the time of hospitalization, 2 weeks after hospitalization, at discharge, and 6 months after hospitalization on predefined outcome variables such as intensity of back and leg pain, Oswestry Disability Index, quality of life, Patient Global Impression of Change, and adverse effects. The protocol of this study was registered in CRIS (KCT0003709) and Clinical trial gov (NCT03750591). This study is significant in that it cannot only be a basis for safety-related evidence of complementary alternative medicine, which has been lacking, but it also gives clear evidence on the effectiveness and validity of treatment effects such as accompaniment of stenosis, sex, age, and type of disc herniation.

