#### Protocol overview

2.1.1

This study is a prospective observational study having a registry and no control group. All treatments during hospitalization will be recorded with no restrictions. We plan on recruiting 1000 patients admitted at 4 spine specialized Korean medical hospitals. Patients enrolled in the registry will be evaluated on predefined outcome variables (pain, quality of life, disability, and physical examination) at the time of hospitalization, 2 weeks after hospitalization, at discharge, and 6 months after hospitalization. The protocol of this study was registered in CRIS (KCT0003709) and Clinical trial gov (NCT03750591).

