### Participating centers

2.2

The subjects will be recruited from 4 spine specialized Korean medical hospitals. To reflect the regional diversity, the study will be conducted in 4 Korean medical hospitals that are distant from each other. All participating centers are spine specialized Korean medical hospitals designated by the Ministry of Health and Welfare, where integrative Korean medicine treatment using acupuncture, herbal medicine, chuna therapy, and pharmacopuncture is performed. Additionally, as doctors practicing Western medicine conduct consultations there, conservative treatments such as injection and physical therapy can be performed.

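### A single uncontrolled cohort cannot show an advantage of adding Western treatment, or different treatment effects by stenosis, age, sex or herniation type; it can show associations and prognostic factors

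*Protocol article*

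**What the plan says.** Protocol overview describes the design: "This study is a prospective observational study having a registry and no control group". The planned size is 1000 patients from four hospitals, and on treatment it says "All treatments during hospitalization will be recorded with no restrictions". Participating centers explains how Western care arises: "as doctors practicing Western medicine conduct consultations there, conservative treatments such as injection and physical therapy can be performed".

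The Discussion concedes that effectiveness data may be limited without a comparison group. In the same paragraph it turns to splits by stenosis and by Western conservative treatment and concludes that "it is possible to analyze the advantages of combination treatment even without the control group". It then says that differences in treatment effect by age or sex can be analysed as well. The Abstract is firmer: the study "gives clear evidence on the effectiveness and validity of treatment effects such as accompaniment of stenosis, sex, age, and type of disc herniation".

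The second of the Secondary objectives is worded differently. It asks which factors affect improvement in patients who received the treatment.

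**The concern.** Two kinds of contrast are presented as informative about treatment effects, and each fails for its own reason.

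- **Western co-treatment.** It is chosen during care, so users and non-users may differ in severity. It starts after admission, so a longer stay gives more opportunity to receive it. Stays of 7 days or less are a withdrawal criterion, which further selects who is compared.
- **Stenosis, age, sex, herniation type.** These are not chosen treatments. The difficulty is that all patients are treated, so a subgroup difference in change need not be a difference in treatment effect.

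At stake is what the registry may conclude. A significant contrast could be published as an advantage of combination treatment, or as differential effectiveness, when neither exists. A large sample does not protect against this; it makes a biased contrast more likely to reach significance.

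**Working it through.** The article gives no effect size, SD or share of patients on Western treatment, so there is no figure to reproduce. Everything numerical below is illustration on assumed inputs. From the document come only n = 1000, the entry threshold of NRS 5 or more for back or radiating pain, and the .05 level (taken as two-sided).

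**1. How a bias becomes a significant result.** Let the true effect be zero and let confounding shift one group's mean by b SD. Then SE = √(1/n₁ + 1/n₂), and the rejection rate is Φ(b/SE − 1.96) + Φ(−b/SE − 1.96). For 500 against 500, SE = √(2/500) = 0.0632. At b = 0.2, b/SE = 3.16 and the rate is Φ(1.20) ≈ 0.885.

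| Split of 1000 | b = 0.1 | b = 0.2 | b = 0.3 |
|---|---|---|---|
| 50:50 | 35% | 89% | 99.7% |
| 30:70 | 31% | 83% | 99% |
| 10:90 | 16% | 48% | 81% |

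**2. Co-treatment driven by admission pain.** The assumed model is:

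- Admission NRS has mean 6.8 and SD 1.3, limited to 5–10.
- Change = −(2.5 + s × (admission − 6.8)) + N(0, 1.6).
- logit P(Western) = −0.4 + a × (admission − 6.8)/1.3.
- The true Western effect is 0, with n = 1000.

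Results for the unadjusted comparison of change between users and non-users:

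| a | s | Limits 5–10 applied by | False benefit (NRS points) | p < .05 |
|---|---|---|---|---|
| 0.8 | 0.5 | clipping | 0.41 | 96% |
| 0.8 | 0.5 | truncation | 0.33 | 86–89% |
| 0.4 | 0.25 | truncation | 0.09 | 12–13% |
| 0.2 | 0.25 | truncation | 0.05 | 8% |

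Ranges reflect simulation error between runs. At a = 0.2 and s = 0.2 the rate is about 6%, close to nominal. The span is thus roughly 7% to 96%, and the top figure is a single strong scenario. In this model, adjusting for admission score returns the bias to about zero and the rejection rate to 4–6%, because that score is the only confounder and is fully measured.

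**3. Co-treatment driven by poor early response.** Keep a = 0.8 and s = 0.5, and let use also rise by 0.4 log-odds per SD of residual change (worse than expected). The unadjusted sign reverses: apparent harm of about 0.16 to 0.23 points, significant in about 31% to 58% of runs. Adjusting for admission score does not repair this. In a check of the same model the adjusted contrast showed about 0.6 points of apparent harm, because the selection happens after admission. This is the reason for a landmark, with outcome taken after it.

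**4. Subgroups.** For subgroup g, the observed mean change is (natural course + regression to the mean)g + (treatment effect)g. The difference between two subgroups is the difference in the first bracket plus the difference in the second. Only the sum is observed, and no untreated patients exist to separate the parts. Entry on high pain makes regression to the mean relevant. The Discussion itself expects some patients with severe initial pain to recover fast and leave early, so prognosis is not uniform. The contrast identifies prognostic factors, as the secondary objective asks, but not effect modification.

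**The case against.** The Discussion speaks conditionally of what is possible to analyse, concedes the missing comparison group, and plans comparison patients through other registries. The secondary objective already uses prognostic wording. All of that is fair. However, the concession is largely taken back in the same paragraph by the statement on combination treatment, and the Abstract carries no such caution.

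Three stronger readings are tempting, and the document does not support them.

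- A reader might infer that stenosis, age and sex are confounded by indication. They are patient characteristics, so that mechanism does not apply.
- A reader might infer that the plan fixes an unadjusted comparison. Statistical analysis assigns no test to these contrasts and allows a linear mixed model, which can carry covariates. The article condenses a fuller plan, so silence on adjustment is not an error.
- A reader might infer that a false positive is nearly certain. The 96% rests on inputs the document does not supply, and weaker ones bring it close to nominal.

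It is also an inference that Western care goes to patients with more pain or slower recovery. The article says only that such care is available through consultations.

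**Conclusion.** The point holds as one about stated conclusions. The design cannot deliver an advantage of combination treatment, or clear evidence on treatment effects by patient characteristics. For co-treatment the threats are confounding by indication and unequal time to be exposed. For the characteristics, the threat is that prognosis cannot be separated from effect modification.

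The size is not determined by the document: about 7% to 96% false significance under the admission-pain model, with a reversed sign when use follows poor early response. These figures rest on assumed strengths of selection and show only that neither size nor direction would be interpretable. The planned before–after analyses are unaffected.

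**What to change.** 1. In the Discussion, replace the statement on combination treatment with one saying that associations between Western co-treatment and outcome will be described and do not estimate the benefit of combination treatment.
2. Define co-treatment by an early landmark (for example, use within the first 3 days), take outcome after it, and adjust in one model for admission score, age, sex, stenosis, herniation type, concomitant disease and centre. State that adjustment removes only measured baseline confounding.
3. Describe age, sex, stenosis and herniation type as prognostic factors for improvement, in line with the secondary objective, and report them with 95% CIs.
4. Remove the promise of clear evidence on treatment effects from the Abstract.

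The cost is wording plus one model on data already being collected. The downside is that the registry claims less.

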#### Primary objectives

2.1.2

The purpose of this study is to prospectively evaluate the efficacy and safety of integrative Korean medicine treatment that uses acupuncture, chuna manual therapy, pharmacopuncture, and herbal medicine on LDH patients.

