**Table 1 T1:**
[figure not shown]
Items to be observed by timepoints.

The items to be surveyed are as follows.

-NRS of waist and legs-Quality of life: EuroQol-5D-5L (EQ-5D-5L)-Oswestry Disability Index (ODI)-Physical examination-Adverse effects are examined daily by the medical staff during hospitalization-All records of medical treatments, both western and Korean, performed during hospitalization of the patients

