#### Follow-up

2.6.3

Follow-up assessment will be conducted from the baseline of the treatment to 6 months after the treatment. Follow-up via phone call will assess NRS of waist and legs, EQ-5D-5L, ODI, and Patient Global Impression of Change .

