### Adverse events

2.7

Adverse events (AEs) are undesirable and unintentional signs (ie, abnormal laboratory test result), symptoms, or disease. The researchers will analyze the frequency of AEs, abnormal blood test results, and severe adverse events. During the inpatient treatment period and telephone follow-up, the researchers will confirm and analyze the presence of AEs.

The staff will determine and record the treatments that are likely responsible for the AEs that have occurred and will evaluate the causal relationship between each treatment method and AEs in a six-stage scale (1 = definitely related, 2 = probably related, 3 = possibly related, 4 = probably not related, 5 = definitely not related, and 6 = unknown).

All AEs will be classified into the following 3 levels by Spilker classification^[12]^:

Mild: When no treatment is required and the side effect does not significantly impair the normal life (function) of the subject; Moderate: When the side effect significantly impairs the normal life (function) of the subject, may require treatment, and can recover after treatment, and Severe: When severe adverse reactions require advanced treatment and may have after effects).

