### Withdrawal and dropout criteria

2.8

At any time during the study, the subject may voluntarily withdraw from the study or be dropped out at the researcher's discretion. If the clinical study is discontinued for the subject, the investigator will assess and record the main cause of the dropout.

1)Patients who have been hospitalized for ≤7 days2)Patients whose guardian or they themselves requests to be withdrawn from the study during the study period or subject withdrawal of consent to participate in the clinical research3)When progress of the research is deemed unsuitable by other investigators4)If the patient is not applicable in at least 1 “selection criterion"5)If the patient is not applicable in at least 1 “exclusion criterion"6)Subjects whose systematic disease was not found in the pre-clinical examination7)If the subject cannot participate in follow-up

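### Late adverse events in dropouts are pursued only where an in-hospital event occurred, so late-event rates are open to selective-ascertainment bias in either direction

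*Protocol article*

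**What the plan says.** Section 2.1.2 puts safety beside efficacy: "The purpose of this study is to prospectively evaluate the efficacy and safety of integrative Korean medicine treatment". Section 2.1.1 sets the recruitment target: "We plan on recruiting 1000 patients admitted at 4 spine specialized Korean medical hospitals".

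AEs are collected in two periods. In hospital, section 2.6.2 says "Adverse effects are examined daily by the medical staff during hospitalization". After discharge, section 2.7 says "During the inpatient treatment period and telephone follow-up, the researchers will confirm and analyze the presence of AEs", and the Abstract lists adverse effects among the outcomes evaluated up to six months. The description of the call in section 2.6.3 is narrower: "Follow-up via phone call will assess NRS of waist and legs, EQ-5D-5L, ODI, and Patient Global Impression of Change".

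Section 2.8 lists, among the withdrawal and dropout criteria, "Patients who have been hospitalized for ≤7 days", and also subjects who cannot take part in follow-up. The main cause of each dropout is to be recorded. The Discussion expects many dropouts because of the short-stay rule and accepts that "the information about the late adverse events in dropout patients is missing" may be a consequence. Its answer is: "We plan on thoroughly reviewing the reasons for dropouts and revisit those patients with adverse effects during hospitalization".

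**The concern.** The recovery step selects on the wrong variable. The gap that the Discussion admits is late events in patients who have left the study. A dropout whose first event starts after leaving had, by definition, no in-hospital event, and so falls outside the group to be revisited. The patients most likely to be missed are those the protocol removes by its own rule: treated, discharged within seven days, and without an event by then.

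This concerns data collection, so it cannot be repaired at analysis. The article presents the registry as a basis for safety evidence that has been lacking. A late-AE rate for which part of the cohort was asked only if an event had already occurred is hard to interpret, whichever denominator is used.

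**Working it through.** The article gives no dropout rate, AE rate or precision basis for 1000, so there is no stated figure to reproduce. What follows is an illustration.

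**Who is asked about late AEs, as written**

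| Group | Stated route |
|---|---|
| In follow-up | Six-month call (section 2.7 and Abstract; AEs not in the section 2.6.3 list) |
| Dropout with an in-hospital AE | Revisited (Discussion) |
| Dropout without an in-hospital AE | None stated |

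**Assumed inputs** (none is in the article)
- d, share of enrolled patients who drop out: 10% to 40%.
- h, share with an in-hospital AE: 10% or 30%.
- r, late-AE risk in patients with an in-hospital AE relative to those without: 1 or 3.
- p, true late-AE risk: 5%, the same in dropouts and completers.

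**Formulas**
- Late risk without an in-hospital AE: b = p / (h·r + 1 − h).
- Late events found, as a share of all enrolled: A = (1 − d)·p + d·h·r·b.
- Share of patients ascertained: S = (1 − d) + d·h.
- Reported rate: A if uncontacted dropouts count as event-free; A/S if only ascertained patients are counted.

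**Worked cases at d = 30%**
- h = 10%, r = 1: b = 5%. A = 0.70 × 5% + 0.30 × 0.10 × 5% = 3.65%, which is 0.73 of the true rate. S = 0.73, so A/S = 5.0%, ratio 1.00.
- h = 30%, r = 3: b = 5% / 1.6 = 3.125%, so risk after an in-hospital AE is 9.375%. A = 3.5% + 0.30 × 0.30 × 9.375% = 4.34%, ratio 0.87. S = 0.79, so A/S = 5.5%, ratio 1.10.

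**Range over the grid** (true rate 5%)

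| Dropout | All enrolled as denominator | Ascertained patients only |
|---|---|---|
| 10% | 4.55–4.78% (0.91–0.96 of true) | 5.00–5.14% (1.00–1.03) |
| 30% | 3.65–4.34% (0.73–0.87) | 5.00–5.50% (1.00–1.10) |
| 40% | 3.20–4.13% (0.64–0.83) | 5.00–5.73% (1.00–1.15) |

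The ratios do not depend on p, which cancels. If late risk also differs between dropouts and completers, the bias can go either way under either denominator.

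**Precision.** For an event never observed, the one-sided 95% upper limit is 1 − 0.05^(1/n): 0.30% for n = 1000, 0.43% for n = 700 and 0.50% for n = 600. The last two correspond to 30% and 40% dropout with no dropout contacted. They show a loss of information, not an under-count.

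**The case against.** The strongest reply is that the authors disclose the problem, and that one Discussion sentence in a condensed article is not the operating procedure. The sentence does not say that other dropouts will not be contacted, and section 2.9 refers to a separate standard operating procedure. This is fair as a limit on certainty. But the sentence is the only AE-recovery step stated for dropouts, and disclosing a gap does not close it when the remedy passes over the patients in whom the gap lies.

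A second reply is that the word chosen for the remedy may mean re-examining records, not contacting patients. On that reading no dropout is asked about late events. The all-enrolled ratio then becomes 1 − d, that is 0.90 to 0.60 for 10% to 40% dropout, so the ambiguity does not help the plan.

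Three stronger readings might be inferred, and the article does not support them:

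- **That patients in follow-up are not asked about AEs.** Section 2.7 and the Abstract both place AE assessment at the six-month contact, and the content of Table 1 is not visible in the text at hand. The list in section 2.6.3 is an inconsistency to align. Still, nothing says that patients withdrawn under section 2.8 receive the call.
- **That the safety rates will be too low.** Inpatient events are checked daily and are untouched by this mechanism. For late events the direction depends on the denominator.
- **That AEs will be reported as crude counts over 1000.** The number 1000 is a recruitment target. No AE denominator and no count-only rule is stated, and exposure-adjusted rates may sit in an analysis plan that is not shown.

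**Conclusion.** The point stands in a limited form. Followed as written, the plan gives first late events no stated recovery route in treated dropouts who had no in-hospital event, and the short-stay rule is expected to create many dropouts. Late-AE rates are therefore open to selective-ascertainment bias: too low if uncontacted dropouts are counted as event-free, possibly too high if only ascertained patients are counted.

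The size is unknown. The ranges of 0.64–0.96 and 1.00–1.15 of the true rate rest on assumed dropout, in-hospital AE share and relative risk, and on equal late risk in dropouts and completers. At r = 1 with only ascertained patients counted, there is no bias, only lost precision.

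This should be changed. It weakens the safety half of the primary objective and cannot be mended later, but it does not invalidate the registry.

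**What to change.** - Keep every treated patient in the six-month call for the same scripted AE question, whether or not an in-hospital event occurred. This includes stays of seven days or less and other dropouts, unless consent is withdrawn. Dropping out of the effectiveness assessments need not end safety follow-up.
- Add AEs to the call content in section 2.6.3, so that it agrees with section 2.7 and the Abstract.
- Report late AEs over the number of patients actually contacted, and show how many treated patients could not be reached.

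The cost is extra calls to dropouts; for patients in follow-up the AE question is already promised. Some dropouts will remain unreachable, recall at six months is imperfect, and the reported AE rate may rise. The change makes being asked independent of an earlier event. It does not remove bias from patients who cannot be reached.
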